## Abstract

**Background:**

Early adolescence is a period of dynamic neurobiological change. Converging lines of research suggest that regular physical activity (PA) and improved aerobic fitness have the potential to stimulate positive brain changes, improve cognitive function and boost academic attainment in this age group, but high-quality studies are needed to substantiate these findings. The primary aim of the Fit to Study trial is to investigate whether short infusions of vigorous PA (VPA) delivered during secondary school physical education (PE) can improve attainment in maths, as described in a protocol published by NatCen Social Research. The present protocol concerns the trial’s secondary outcome measures, which are variables thought to moderate or mediate the relationship between PA and attainment, including the effect of the intervention on cardiorespiratory fitness, cognitive performance, mental health and brain structure and function.

**Method:**

The Fit to Study project is a cluster-randomised controlled trial that includes Year 8 pupils (aged 12–13) from secondary state schools in South/Mid-England. Schools were randomised into an intervention condition in which PE teachers delivered an additional 10 min of VPA per PE lesson for one academic year, or a ‘PE as usual’ control condition. Intervention and control groups were stratified according to whether schools were single-sex or co-educational. Assessments take place at baseline (end of Year 7, aged 11–12) and after 12 months (Year 8). Secondary outcomes are cardiorespiratory fitness, objective PA during PE, cognitive performance and mental health. The study also includes exploratory measures of daytime sleepiness, attitudes towards daily PA and PE enjoyment. A sub-set of pupils from a sub-set of schools will also take part in a brain imaging sub-study, which is embedded in the trial.

**Discussion:**

The Fit to Study trial could advance our understanding of the complex relationships between PA and aerobic fitness, the brain, cognitive performance, mental health and academic attainment during adolescence. Further, it will add to our understanding of whether school PE is an effective setting to increase VPA and fitness, which could inform future PA interventions and education policy.

**Trial registration:**

ClinicalTrials.gov, NCT03286725. Retrospectively registered on 18 September 2017.

ClinicalTrials.gov, NCT03593863. Retrospectively registered on 19 July 2018.

**Electronic supplementary material:**

The online version of this article (10.1186/s13063-019-3279-6) contains supplementary material, which is available to authorized users.

## Background

Early adolescence is a period of dynamic neurobiological and psychological change [1] and provides a foundation for future health [2]. Understanding how health and education policies might steer the developmental course in a positive direction is therefore important [3].

Converging lines of research suggest that physical activity (PA) and aerobic exercise have the potential to stimulate positive brain changes, improve cognitive function and boost academic attainment in this age group. Neuroscience studies using animal models have indicated that, at the molecular level, aerobic exercise increases levels of growth factors responsible for synaptic plasticity, particularly in the hippocampus [4, 5]. At the cellular level, increased growth factor production is thought to promote the development of new blood vessels and neurons and their integration into existing networks of cells in this region [6]. Neuroimaging studies in adults [7], and increasingly in children [8, 9], have found support for PA and fitness-related changes in brain function and structure. For instance, hippocampal volume is larger in higher fit children and may mediate the relationship between fitness level and memory outcomes [10].

Meanwhile, intervention studies in schools have found some evidence that programmes of aerobic exercise can lead to improved cognitive performance, particularly in the domains of attention and executive functions (working memory, cognitive flexibility, and inhibitory control) [11–17]. Separately, there are associations between objectively measured PA and academic attainment among adolescents [18] and indications that school-based exercise interventions can improve educational outcomes in this age group [9, 19]. The balance of evidence among adolescents favours positive associations between aerobic exercise, fitness, cognition and attainment [20], although the variety of study designs, including different types, intensities and durations of PA, makes firm conclusions difficult to draw.

The benefits of PA for physical and mental health are well known [21, 22], yet PA levels among young adolescents are low [23] and continue to decline during early adolescence [24]. Adolescence is also a peak time for the onset of mental ill-being, including vulnerability to low self-esteem [25, 26]. There is some evidence that physical health and mental well-being and ill-being are also linked with academic attainment [27, 28], but whether these factors act as mediators in the relationship between PA and academic attainment is currently unclear.

School is a recommended setting for promoting PA among adolescents, including those from lower socio-economic backgrounds, because they spend a large proportion of their time at school and interventions can be delivered without relying on support from families [29]. There is evidence that physical education (PE) interventions to increase activity are an effective method of improving cognitive function and academic performance [11, 19]. However, less than 50% of a typical PE lesson is spent in moderate-to-vigorous PA (MVPA), the type of activities that noticeably accelerate the heart rate [30, 31]. Short bouts of high-intensity or vigorous physical activity (VPA), during which individuals work at around 80% of their maximum heart rate for between 45 s and 4 min, have been shown to deliver equivalent fitness benefits to longer, lower-intensity workouts [32, 33]. This type of vigorous activity is brief enough to be incorporated into PE lessons without disrupting curriculum delivery, and there is evidence that it can improve adolescent fitness [34, 35].

The primary aim of the trial is to investigate the impact of a 1-year VPA intervention (Fit to Study) delivered during PE on maths attainment. To date there is little school-based evidence to test whether relationships between PA and academic achievement among young adolescents are mediated or moderated by fitness, cognitive function, mental health outcomes and/or the brain. The secondary aim of this trial is therefore to investigate whether the intervention improves fitness, cognitive performance and mental health outcomes, and changes brain structure and function, compared to usual PE lessons delivered over a school year, and to further explore relationships between these measures.

### Hypotheses

The primary hypothesis for the trial is:A programme of VPA, delivered during PE lessons for one academic year (10 months), will improve maths attainment at the end of the intervention in the intervention group relative to the control group.

The secondary hypotheses are:2.The intervention will increase VPA during PE, and fitness levels, of pupils in the intervention group relative to the control group.3.The intervention will improve cognitive performance (processing speed, memory and executive functions) in the intervention group relative to the control group.4.The intervention will improve physical and mental health outcomes in the intervention group relative to the control group.5.The intervention will change brain structure and function in the intervention group relative to the control group.

## Methods and analysis

### Design

The study is a parallel group, superiority cluster-randomised efficacy trial of a one academic year (10-month) VPA intervention versus control. Clusters are secondary state schools in South/Mid-England; participants are Year 8 pupils within those schools. The intervention is incorporated into PE lessons to minimally disturb the curriculum and provide a scalable intervention that could be easily implemented in regular school PE lessons. Trial data are collected at baseline (end of Year 7, pupils aged 11–12) and after 12 months (end of Year 8, pupils aged 12–13). Figure 1 presents an overview of the schedule for enrolment, the intervention and the assessments, according to the Standard Protocol Items: Recommendations for Interventional Trials (SPIRIT) guidelines (Additional file 1).

**Fig. 1 Fig1:**
[figure not shown]
Fit to Study trial schedule of forms and procedures (adapted from SPIRIT figure). Abbreviations: *HBSC* Health Behaviour in School-aged Children, *PDSS* Paediatric Daytime Sleepiness Scale, *PE* physical education, *P-SDQ* Physical Self-Description Questionnaire, *SDQ* Strengths and Difficulties Questionnaire, *PA* physical activity, *VPA* vigorous physical activity

A sub-set of pupils from a sub-set of schools will also take part in a brain imaging sub-study which is embedded in the trial. Data for the brain imaging sub-study are collected at baseline (end of Year 7, pupils aged 11–12), after 12 months (end of Year 8, pupils aged 12–13) and at 24 months (end of Year 9, pupils aged 13–14).

The trial has been approved by the Central University Research Ethics Committee of Oxford University (Registration No. R48879). The main trial protocol was retrospectively registered at ClinicalTrials.gov on 18 September 2017 (NCT03286725). At this time, study enrolment was complete and data acquisition was in progress. The brain imaging sub-study protocol was retrospectively registered on 19 July 2018 (NCT03593863). At this time study enrolment and data acquisition were both still in progress. The primary measure, attainment in maths, is recorded separately on the ISRCTN registry (15730512).

### Independent evaluation

The trial will be independently evaluated by NatCen Social Research. NatCen performed the randomisation and the trial’s power calculation, and will carry out the primary intention-to-treat analysis, comparing maths performance between intervention and control schools. The protocol and statistical analysis plan for the independent evaluation has been published separately [36, 37].

### Sample selection and recruitment

A total of 106 schools have been recruited and assessed for eligibility (Fig. 2). To be eligible, schools must (1) be secondary state or academy schools, but not grammar schools; (2) be mixed or single-gender; (3) have a proportion of pupils eligible for free school meals (FSM), preferably more than 15%, which is the average for England (at the time of recruitment [36]); (4) be located within a pre-defined set of local authorities, encompassing the following geographical locations: Greater London; Thames Valley; Southampton and Portsmouth; Bristol and Bath; Birmingham and Coventry; Cheltenham/Gloucester; Luton, Bedford Milton Keynes; (5) have Year 7 pupils who will move on to Year 8 at the start of the intervention; (6) deliver PE as part of their curriculum; (7) sign an agreement to send opt-out consent forms to parents/carers of Year 7 pupils and inform the research team of pupils who have opted out of data storage. Following the eligibility assessment, two schools declined to participate. Of the remaining 104 schools, all pupils in Year 8 at the start of the intervention (academic year 2017–2018) are part of the trial, given that project activities are classed as part of regular school activities. However, pupils who opted out of data storage are not required to participate in any of the trial’s assessments, unless decided otherwise by the PE teacher.

**Fig. 2 Fig2:**
[figure not shown]
Flow diagram of schools and participants. ^1^A total of 104 schools were randomised into an intervention and a control group. Prior to baseline assessments, 11 schools dropped out. Schools were informed of their assigned group by the research team after completing baseline assessments

The National Foundation for Educational Research (NFER) led recruitment, supported by Oxford Brookes University. The NFER initially sent recruitment materials to 1125 schools, and, to improve response numbers, widened their search area to include another 223 schools. Recruitment presentations were given at County PE Teacher Conferences organised by the Oxfordshire Sports Partnership and the Buckinghamshire and Milton Keynes Sport and Activity Partnership. Those schools that wished to participate and met the inclusion criteria provided the names, dates of birth, genders, FSM status and unique pupil numbers (UPNs) of all Year 7 pupils. Schools were considered formally recruited upon transfer of the data to the NFER.

### Randomisation

Schools (*n* = 104) were randomised into an intervention group or control ‘PE as usual’ control group using stratified block randomisation and an allocation ratio of 1:1 (Fig. 2). Stratification was arranged by single-sex/co-educational status of schools. NatCen performed the randomisation using a random number generator in STATA (v.12) [36, 37]. To reduce the risk of bias, schools were informed of their assigned group by the research team after completing baseline assessments.

### Intervention

The intervention consisted of a one academic year (10 months: September 2017–June 2018) PA programme delivered by PE teachers during regular Year 8 PE lessons. In the summer term prior to the trial, Year 8 PE staff from all intervention schools were invited to attend a 2-h face-to-face training session delivered by a team from Oxford Brookes University who designed the intervention. Those unable to attend were asked to join an interactive 2-h online training session delivering the same content. Teachers unable to take part during the summer term attended training at the start of the autumn term. During these sessions, the intervention was described to the teachers.

The intervention requires teachers to deliver specific elements of additional VPA, over and above normal VPA, during all Year 8 PE lessons, for the whole school year. Four minutes of VPA are incorporated into the PE lesson as part of a warm-up, and three 2-min infusions per hour of PE are incorporated into the main PE class. In this study, VPA is defined as activities that raise the heart rate (HR) to 71–85% of the maximum HR (HRmax), whereas moderate PA raises it to 60–70% of HRmax. The intervention elements are designed to be easy to incorporate into PE lessons, to maximise the training effect and to minimise the risk of injury with a warm-up that progresses from light to moderate-intensity activities and includes bursts of VPA.

Teachers were asked to deliver an active 10-min warm-up at the start of each lesson, beginning with light-intensity movements (e.g. wrist rotations; leg swings) and moving through moderate-intensity activity (e.g. arm rotations; walking with high knee-raise) to incorporate two periods of VPA (e.g. vigorous arm sprints; running on the spot) totalling 4 min. Fifteen young adolescents piloted the warm-up and the infusions while wearing chest strap Polar heart rate monitors, which indicated that heart rates were in the vigorous zone for the specified time during all the intervention elements.

In addition, three 2-min infusions of VPA would be incorporated into the main PE lesson, assuming a 1-h lesson duration. If lessons were shorter or longer than 1 h, then the number of infusions was scaled up or down accordingly. Teachers were provided with three example infusions: infusion 1 consisted of fast arm rotations (the aim is to build the intensity by speeding up arm movements concluding with two maximum effort sprints for counts of ten); infusion 2 comprised squats and lunges with an emphasis on technique and a full range of motion (to work the muscles to the maximum, concluding with a maximum effort sprint on the spot for a count of ten); and infusion 3 was sprinting on the spot (this must be completed at a vigorous intensity with the two ‘on the spot’ sprint sessions lasting for counts of ten), with active recovery periods where necessary during each 2-min session. Teachers were also invited to create their own warm-up and/or infusions to provide similar levels of VPA to fit their lesson requirements. Researchers explained the rationale for the intervention and discussed implementation strategies.

Teachers were given access to video demonstrations of the warm-up and infusion material on the trial’s website. Heads of PE at intervention schools received emails reminding them to deliver the intervention in September and December 2017 and in February 2018. Researchers visited 30 intervention schools between September and December 2017 to answer questions and offer support and advice. PE staff were invited to join an online intervention discussion forum, and schools were offered the chance to have intervention lessons filmed. Researchers were also available to answer email and phone queries. Control schools were not given training and were asked to deliver PE as usual. During the intervention period, heads of PE in these schools received emails in September 2017 and February 2018 with information about testing. School participation was incentivised to minimise drop-out and ensure compliance. Both intervention and control schools receive £500 upon completion of the trial, following the academic attainment assessment.

### Intervention fidelity

All Year 8 PE teachers in intervention schools were asked to keep a written log of VPA achieved in each PE lesson. Specifically, they were asked to record whether the class completed 4 min of VPA during the warm-up and to mark how many infusions were delivered. Teachers were informed that for a teacher-created warm-up to be marked as completed, it must have lasted 10 min and progressed from light-intensity small movement activities to larger moderate-intensity activities with short bursts of vigorous-intensity activities. For a teacher-created infusion to be marked as completed, it must have lasted 2 min and included two short bursts of VPA (or equivalent, as per infusion 2, described in the ’Intervention’ section).

Further, researchers are visiting a convenience sample of intervention and control schools during 2018 to take objective measurements of PA during PE using Axivity AX3 accelerometers (see ‘Physical activity during PE’ in the subsequent section ‘Secondary outcome measures’). Finally, a subjective measure of compliance will be collected from participants from all schools during post-intervention testing using a brief three-item survey asking whether (1) PE lessons start with a warm-up, (2) PE lessons include bursts of VPA that raise their heart rate and make them feel out of breath and (3) participants take part in warm-ups or VPA bursts if asked by PE teachers.

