##### Physical activity during PE

Objective measures of VPA during PE are being collected in each school once during regular lessons at baseline (May–July 2017, and at some remaining schools in September 2017) and again during lessons in spring term (March–May 2018). Each school is visited at each timepoint to test at least 50% of the pupils in the year group. Measures are taken using the Axivity AX3, a wrist-worn tri-axial accelerometer designed by Open Lab, Newcastle University, UK. Trained research assistants show pupils how to fit the AX3 on their non-dominant wrist. The devices are attached after pupils change for PE and collected before they change back into school clothes. Class average minutes of MPA and VPA during active lesson time are calculated using established cut-points [68] and standardised, for comparison purposes, to minutes per hour.

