### Data analysis plan

In accordance with the Consolidated Standards of Reporting Trials (CONSORT) 2010 statement for cluster-randomised controlled trials guidelines [85], the cluster and participant flow will be reported. Descriptive statistics of recruitment and drop-out will be provided on both the cluster and subject levels. Further, completeness of, and adherence to, the intervention will be reported on a cluster-level only. Baseline characteristics of the randomised groups will be summarised across schools and/or pupils, and will be presented on a pupil level where appropriate.

The primary intention-to-treat analysis comparing maths test performance between intervention and control schools will be conducted by NatCen and is described elsewhere [37]. To account for differences between pupils at baseline, baseline maths performance (Key Stage 2 test score) will be collected from the National Pupil Database (NPD). Analysis of secondary outcome measures will be conducted on an intention-to-treat basis. Per-protocol analyses of secondary measures will also be reported.

Multilevel modelling will be used, as these analyses take the hierarchical structure of the data into account (i.e. pupils within schools) [86]. The models will be used to assess the effect of the intervention, as well as to explore associations between secondary outcome measures, and will adjust for various confounding factors (e.g. sex, socio-economic status, school gender status). Structural equation models (SEMs) may be used for mediation analyses.

MRI data collected as part of the brain imaging sub-study will be analysed and processed using tools from MrTrix3, MATLAB, the FMRIB Software Library (FSL), statistical parametric mapping (SPM) and FreeSurfer, employing parametric and non-parametric statistical analysis methods where appropriate. Details of data (pre) processing and analysis are provided in Additional file 2.

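### The accelerometer measure of VPA during PE has two incompatible sampling rules and two blinding statuses, so it is unclear which schools test the VPA part of hypothesis 2

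*Protocol article*

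**What the plan says.** All references are to the Protocol article.

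- **Intervention fidelity:** "researchers are visiting a convenience sample of intervention and control schools during 2018 to take objective measurements of PA during PE". The sentence goes on to name the instrument and to point elsewhere for detail: "using Axivity AX3 accelerometers (see ‘Physical activity during PE’ in the subsequent section ‘Secondary outcome measures".
- **Physical activity during PE**, the section pointed to: "Objective measures of VPA during PE are being collected in each school once during regular lessons at baseline". It adds a second round in March to May 2018 and then states the coverage: "Each school is visited at each timepoint to test at least 50% of the pupils in the year group".
- **Abstract, Method:** "Secondary outcomes are cardiorespiratory fitness, objective PA during PE, cognitive performance and mental health".
- **Hypotheses**, number 2: "The intervention will increase VPA during PE, and fitness levels, of pupils in the intervention group relative to the control group".
- **Data analysis plan:** "Analysis of secondary outcome measures will be conducted on an intention-to-treat basis".
- **Blinding:** researchers who assess secondary outcomes do not know a school's arm. Those who visit to collect fidelity measures and give top-up training do know it.

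**The concern.** A named secondary outcome should have one stated rule for which clusters are measured and one statement of who measures them blind. Here the same data are introduced once as a fidelity check in conveniently chosen schools and once as an outcome taken everywhere.

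This matters because of the measure's role. It is the only objective evidence in the main trial that PE lessons in intervention schools contained more VPA than those in control schools. The teacher logs are kept in intervention schools only, and the pupil compliance survey is self-report. If measured schools were picked for convenience, the intervention and control schools with data need not be comparable, even though the full set of schools was randomised. A general promise of intention-to-treat analysis would then lead a reader to assume coverage that the outcome does not have.

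**Working it through.** The plan gives no figure to reproduce on this point, so the check is a comparison of text.

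**Step 1. Is it one measurement?**

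| Feature | Intervention fidelity | Physical activity during PE |
|---|---|---|
| Device | Axivity AX3 | Axivity AX3 |
| Setting | PE lessons | PE lessons |
| Timing of later round | during 2018 | March to May 2018 |
| Schools | convenience sample, both arms | each school, both timepoints |
| Role | fidelity | secondary outcome |

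The 2018 windows overlap, and the first section cross-refers to the second by name. They describe the same measurement, and the entries for schools disagree.

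**Step 2. Which blinding statement applies?** Classed as a secondary outcome, the measure is collected by blinded staff. Classed as fidelity, it is collected by unblinded staff. The article classes it as both.

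**Step 3. What follows under each rule?**

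- *Every school is measured.* The Intervention fidelity sentence is wrong. Coverage is then limited only by drop-out: the flow diagram note gives 104 schools randomised and 11 lost before baseline assessments, so at most 104 − 11 = 93 could have been measured at baseline.
- *Only a convenience sample is measured.* The coverage sentence in Physical activity during PE is wrong or incomplete. The VPA comparison then covers a subset whose selection is not described, and the intention-to-treat sentence needs a qualification for this outcome.

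One of the passages must change under either rule.

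**Step 4. Can a size be given?** Not for bias: the article states neither how many schools are in the convenience sample nor how they were chosen. Only the loss of precision can be illustrated, on assumptions. Take one class-average value per school, the same between-school spread and the same split between arms. Take a full set of 106 − 18 = 88 schools (recruited minus drop-outs, from the Sample size section). The standard error then grows by √(88/J) when J schools are measured:

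- J = 60: √(88/60) = 1.21
- J = 40: √(88/40) = 1.48
- J = 20: √(88/20) = 2.10

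These values of J are assumed. The factors say nothing about selection, which is the main issue.

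**The case against.** The best defence is that the two sections can be read together. Intervention fidelity sets the frame, and each school then means each school in that frame. The authors do refer to all schools when they describe the pupil survey in the next sentence, which suggests that they saw the contrast. That reading is possible, but Physical activity during PE states no such limit. Adopting it also concedes the point, because the VPA outcome then does rest on a conveniently chosen subset.

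A second defence is that, if the same schools were measured at both rounds, they were first visited before they were told their arm. That would make selection by expected delivery less likely. It has some force, but Intervention fidelity mentions only 2018, so the text does not settle it.

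A reader might go further and infer that the measure overstates the VPA delivered, on the ground that willing hosts are good deliverers. The documents do not support a direction. They give no reason for the choice of schools, which could be distance or timetable. The unblinded visitors also give top-up training, so visits could lean towards weak deliverers. Control schools are sampled too. Any percentage overstatement would depend on delivery rates that appear nowhere in the article.

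A reader might also infer that the comparison is neither randomised nor by intention to treat. That is too strong. Schools can still be analysed in their allocated arm, with some clusters unmeasured. What is lost is coverage of all randomised schools, and with it the assurance that the arms are comparable.

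**Conclusion.** The concern holds as an inconsistency that has to be resolved. One secondary outcome has two sampling rules and, through the Blinding section, two blinding statuses. This rests on reading the two sections as one measurement, which the device, setting, timing and cross-reference all support.

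If the convenience rule is the true one, the VPA comparison covers a non-randomly chosen subset of the randomised schools and may be biased upwards or downwards. The documents allow no estimate of that bias.

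The reach is limited. The fitness part of hypothesis 2 is tested by PE teachers in their own lessons and is unaffected. The primary maths analysis is run by the independent evaluator under a separately published plan and is also unaffected. Teacher logs and the pupil survey remain as further, non-objective evidence on delivery.

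**What to change.** Reconcile Intervention fidelity, Blinding and Physical activity during PE, so that they give one rule for which schools are measured at each timepoint and one statement of whether those collecting the data know the arm.

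- **If every participating school is measured:** delete the reference to a convenience sample.
- **If only a subset is measured:**
  - Say how schools were chosen. Where visits remain and it is still feasible, draw the remaining schools at random within arm and single-sex/co-educational stratum. Collection was already under way when the article was written, so this may no longer be possible.
  - Report schools measured out of schools randomised, by arm and timepoint.
  - Compare measured with unmeasured schools on baseline characteristics, such as single-sex status, free-school-meal share and baseline fitness. The all-school pupil compliance survey can be shown alongside, but only descriptively. It is collected after the intervention and lies close to the outcome, so it is a poor basis for weights.
  - Describe the VPA result as an as-allocated comparison restricted to measured schools, and not as an intention-to-treat result for all randomised schools.

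The cost is a few sentences of protocol wording, a little extra reporting and a slightly weaker stated claim for this outcome.
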